## Abstract

**Background:**

Post-stroke cognitive impairment (PSCI) is common. However, the underlying pathophysiology remains largely unknown. Understanding the role of microvascular changes and finding markers that can predict PSCI, could be a first step towards better screening and management of PSCI. Capillary dysfunction is a pathological feature of cerebral small vessel disease and may play a role in the mechanisms underlying PSCI. Extracellular vesicles (EVs) are secreted from cells and may act as disease biomarkers. We aim to investigate the role of capillary dysfunction in PSCI and the associations between EV characteristics and cognitive function one year after acute ischemic stroke (AIS) and transient ischemic attack (TIA).

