## Introduction and rationale

We continue to live longer, and the impact of age-related diseases such as stroke and dementia is growing [1]. In addition to the functional disability a stroke may cause, cognitive impairment after stroke is common. Post-stroke cognitive impairment (PSCI) is observed in up to 50% of stroke survivors, and a stroke doubles the risk of dementia [2–4]. Persistent cognitive impairment has also been found in patients with transient ischemic attack (TIA) [5], a disorder that is considered reversible by definition.

PSCI and dementia are associated with increased morbidity and mortality [6–8], however no specific disease modifying management exist. This has urged stakeholders to call for more research into the epidemiology, risk-factors, biomarkers, and mechanisms underlying PSCI [9, 10].

Many risk factors for PSCI have been identified including stroke severity, lesion size and location and common vascular risk factors such as age, hypertension, diabetes, atrial fibrillation, and smoking [5, 11–13]. Further, some magnetic resonance imaging (MRI) markers have been associated with PSCI including brain atrophy and markers of cerebral small vessel disease (cSVD) such as white matter hyperintensities and cerebral microbleeds [14, 15]. In addition, several blood-derived biomarkers have also shown promise as predictors of PSCI [16–18]. Despite these advances in the field, the exact underlying pathophysiology behind PSCI is not well understood. Identification of early pathologic changes associated with PSCI could be a first step in the development of a prognostic aid and in identifying future therapeutic targets.

Cerebral capillary dysfunction is characterized by limited oxygen extraction from the brain capillaries due to age- and risk factor-related capillary flow heterogeneity [19]. Capillary dysfunction is a pathophysiological feature of cSVD and may play an important role in the vascular mechanisms underlying PSCI [20, 21]. Advanced perfusion magnetic resonance imaging (MRI) techniques can detect and quantify capillary dysfunction and may help identify markers of PSCI [22–24].

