### Magnetic resonance imaging

An MRI is performed at 24 h (+/- 6 h) after the acute MRI on admission and again at the 12-month follow-up visit. MRI sequences include T1-weighted 3D images for co-registration, DWI, kurtosis diffusion imaging, 3D fluid-attenuated inversion recovery (FLAIR), susceptibility weighted imaging (SWI), and gradient echo (GRE) and spin echo (SE) perfusion imaging.

White matter hyperintensities, visible on FLAIR images, are semi-automatically outlined [31]. Capillary function is characterized by capillary transit time heterogeneity (CTH), parameterized as the standard deviation of blood transit times within each image voxel using SE perfusion imaging [19, 22, 23]. Finally, grey and white matter microstructural integrity, including dendrite density, axonal density and dispersion, and intra- and extra-axonal water diffusivity are characterized based on DWI and kurtosis diffusion imagning [32–35]. All MRI scans are performed on site with a 3T Siemens Magnetom Vida scanner (Siemens Healthcare, Erlangen, Germany).

The burden of cSVD is assessed on the 24-hour and the 12-month MRI scans. A total cSVD score is calculated based on the STRIVE-1 criteria with local specifications [36]. The cSVD score includes number and location of microbleeds, superficial siderosis, number of lacunes, grade of white matter hyperintensities, grade of global cortical atrophy, and enlarged perivascular spaces. Scoring is independently performed by a trained neurologist and a neuroradiologist. At scoring disagreement, consensus is achieved. Table 3 presents an overview of the used MRI sequences.

**Table 3 Tab3:** MRI sequences and characteristics at 24 h and 12 months

Sequence	Description	Purpose
DWI + ADC	Diffusion Weighted Imaging (DWI) and calculated Apparent Diffusion Coefficient (ADC)	Grey and white matter microstructural integrity, including dendrite density, axonal density and dispersion, and intra- and extra-axonal water diffusivity
Kurtosis	Kurtosis diffusion Imaging	
3D FLAIR	3-Dimensional Fluid-Attenuated Inversion Recovery	White matter hyperintensities, perivascular spaces, and lacunes
3D T1 (MP2RAGE)	3-Dimentional T1- magnetization Prepared Rapid Gradient Echo	Atrophy/cortical thickness
SWI	Susceptibility Weighted Imaging	Microbleeds and superficial siderosis
PWI GRE	Gradient Echo Perfusion Imaging	Capillary transit time heterogeneity
PWI SE	Spin Echo Perfusion Imaging	

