### Statistical analysis

The role of capillary dysfunction on PSCI will be assessed by the association between CTH at baseline and PSCI. The primary outcome will be the difference in total RBANS score from three to 12 months follow-up. Secondary outcomes include total RBANS score at 12 months follow-up, difference in MoCA score from three to 12 months follow-up, and MoCA score at 12 months follow-up. All associations will be assessed using linear mixed effects models adjusting for age, sex, educational level, baseline NIHSS, smoking, and diabetes. Analyses will be stratified by APOE genotype (ε4 carriers vs. non-carriers) and pre-stroke cognitive decline (IQCODE > 3.48 vs. IQCODE ≤ 3.48) to assess for effect modification by these factors. Level of cSVD will be assessed as a mediator.

Associations between EV characteristics and cognitive function after stroke will be assessed primarily by exploring differences in EV characteristics at baseline between patients with normal cognition, impaired cognitive function (total RBANS index score 70–85) and reduced cognitive function (total RBANS index score < 70) at 12-month follow-up using analysis of differential expression. Secondary analyses include exploring differences in EV characteristics at baseline among patients with a decline (≥ 6 points) versus patients with no decline in total RBANS score from three to 12 months, between patients with decline (≥ 2 points) versus no decline in MoCA score from three to 12 months follow-up, and between patients above and below MoCA score of 22 and 26 at 12-months follow-up. Analyses will be adjusted for age, sex, educational level, baseline NIHSS, diabetes, and hypertension. In addition, analyses stratified by APOE genotype, pre-stroke cognitive decline, and level of cSVD will be performed.

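### cSVD is named only as a mediator of baseline CTH, with no scan specified and no CTH model adjusting for it as a confounder, so confounding by cSVD could be reported as an indirect effect

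*Protocol article*

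**What the plan says.** The Statistical analysis section of the protocol article takes baseline CTH as the exposure: "The role of capillary dysfunction on PSCI will be assessed by the association between CTH at baseline and PSCI". The primary outcome is the change in total RBANS score from three to 12 months. The models adjust for age, sex, education, baseline NIHSS, smoking and diabetes. cSVD is not in that list. Its only role in the CTH analysis is given in one sentence: "Level of cSVD will be assessed as a mediator".

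Under Magnetic resonance imaging, the timing is: "An MRI is performed at 24 h (+/- 6 h) after the acute MRI on admission and again at the 12-month follow-up visit". Baseline CTH therefore comes from the 24-h scan. For cSVD the same section says: "The burden of cSVD is assessed on the 24-hour and the 12-month MRI scans". The score combines microbleeds, superficial siderosis, lacunes, white matter hyperintensities, cortical atrophy and perivascular spaces.

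On how the two relate, the abstract says "Capillary dysfunction is a pathological feature of cerebral small vessel disease", and the Introduction says "Capillary dysfunction is a pathophysiological feature of cSVD and may play an important role in the vascular mechanisms underlying PSCI". The Introduction also lists markers of cSVD among the imaging findings associated with PSCI. The Discussion treats it as established that cSVD raises the risk of cognitive impairment and dementia.

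**The concern.** A mediator has to come after the exposure and before the outcome. Neither available cSVD score clearly does.

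- **24-h score.** It is read from the same scan as CTH. It counts structural lesions that were largely present before the stroke, so the data cannot show that CTH came first.
- **Raw 12-month score.** It is measured after CTH, but it includes every lesion already there at 24 h. It is also taken when the outcome window closes.

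The article's own account links cSVD both to capillary dysfunction and to poor cognition. That is the profile of a possible common cause. With CTH and cSVD measured together, a mediator model and a confounder model fit equally well, yet only the mediator reading is stated. If cSVD is the common cause, the CTH association shows only that CTH marks cSVD, and the share labelled as mediated is confounding. This bears on the first primary objective and on the stated hope of learning about microvascular mechanisms.

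**Working it through.** **The plan's own figure.** The Sample size calculation gives 71 patients for 10 predictors, 90% power and a significance level of 0.05. It does not state the effect size, so the figure cannot be reproduced independently. Solving backwards with 10 numerator and 60 denominator degrees of freedom gives f² = 0.335 (R² = 0.25), which is plausible. The present point does not depend on it. The calculations below use the target of 100 patients with complete follow-up.

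**Inputs.** N = 100 and 10 predictors come from the article. The correlations do not, and are assumptions: cSVD with CTH (ρ) 0.3 to 0.5, and cSVD with the outcome (g) 0.3 to 0.4 in absolute value. The simulation also used g = 0.2.

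**Step 1: spurious correlation.** Let cSVD be a pure common cause and the true CTH effect be zero. The CTH–outcome correlation is then ρ × g:
- 0.3 × 0.3 = 0.09
- 0.4 × 0.3 = 0.12
- 0.5 × 0.4 = 0.20

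**Step 2: how often it would be significant.** This treats the value as a partial r, with f² = r²/(1 − r²), 1 and 89 degrees of freedom, and noncentrality f² × 100:

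| r | f² | Chance of p<0.05 |
|---|---|---|
| 0.09 | 0.0082 | 15% |
| 0.12 | 0.0146 | 22% |
| 0.20 | 0.0417 | 52% |

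With noncentrality f² × 91 (numerator plus denominator degrees of freedom plus one), the figures are 14%, 21% and 49%.

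**Step 3: what mediation by the 24-h score would show.** In standardised units, the CTH–cSVD path is ρ, the cSVD–outcome path given CTH is g, and the direct effect is 0. The indirect effect is ρ × g, which is the whole spurious association. A simulation at N = 100 (3,000 runs per scenario, least squares, no further covariates, joint-significance test) agrees. The indirect share was 97% to 101%, the spread around 100% being simulation error, and it was significant in 40% to 95% of runs.

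**Step 4: what a raw 12-month score would show.** Assume it correlates s = 0.9 with the 24-h score. The indirect share is s²(1 − ρ²)/(1 − s²ρ²):
- ρ = 0.3: 0.81 × 0.91 / (1 − 0.0729) = 0.7371 / 0.9271 = 0.80
- ρ = 0.5: 0.81 × 0.75 / (1 − 0.2025) = 0.6075 / 0.7975 = 0.76

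The simulation gave 75% to 83%, significant in 31% to 88% of runs. Using the later score shrinks the problem but does not remove it.

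**The case against.** A reader might infer that the plan has chosen the 24-h score as mediator and that confounding will therefore be reported as mechanism. The documents do not support that. The mediation sentence names no scan, cSVD is scored at both times, and an analysis of cSVD change would fit the present wording. A condensed article may also leave the choice of scan to a fuller document.

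The authors' causal order is arguable too. The Introduction attributes capillary dysfunction to age and risk factors, and age, smoking and diabetes are in the models. The Discussion speaks of detecting preclinical manifestations, which suggests that CTH comes before visible lesions. Calling capillary dysfunction a feature of cSVD does not say that lesions cause it, and capillary dysfunction may itself predate the scan.

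A mediation analysis using the 24-h score would also yield a direct effect of CTH adjusted for cSVD. Much of the requested adjustment could come from it.

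The magnitude is open to challenge: every correlation is assumed, the covariates may absorb part of the cSVD–CTH link, and nothing in the article supports a cSVD correlation of 0.3 to 0.4 with change in RBANS rather than its level.

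All of this stands, and it limits the point to what could happen. It does not settle the order of CTH and cSVD, and it does not make a raw 12-month score a clean mediator. One further inference should be resisted: using cSVD as a stratifier in the EV analyses is no contradiction, since those have a different exposure and question.

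**Conclusion.** The point holds as a limit on what can be concluded, not as an error in the main model. The article gives cSVD a mediator role without naming the measurement, and it states no CTH model that treats cSVD as a confounder. Its own description makes that role as plausible as mediation. Confounding could therefore be presented as an indirect effect; the documents do not show that it would be.

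Under the assumed correlations and no true CTH effect, the spurious association is 0.09 to 0.20, nominally significant in roughly 15% to 52% of studies at N = 100. The upper figure belongs to the most unfavourable pair of assumptions. Both ends ignore the planned covariates and the change outcome. The mediation analysis is subsidiary, and neither the primary outcome nor the sample size is affected. This is a worthwhile, inexpensive improvement.

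**What to change.** - State the assumed causal order and which cSVD measurement each analysis uses.
- Report the CTH association in two pre-stated models, without and with the 24-h cSVD score as a covariate. Claim a capillary role independent of cSVD only if it holds in the second.
- Do not interpret an indirect effect through the 24-h score as mechanism.
- If mediation is kept, use cSVD change from the 24-h to the 12-month MRI, adjusted for the 24-h score, and label it exploratory. Change still runs to the end of the outcome window, which is one reason for that label.

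The cost is some wording and one extra model, since both scores are already planned. The drawback is that the adjusted estimate is conservative if cSVD truly lies downstream of CTH, which is why both models should be shown.

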## Blood samples, EV characterization, and genotyping

At 24 h (+/- 8 h) after admission and at the three-month follow-up visit, a blood sample consisting of three 3.5 mL citrate collection tubes is drawn by study personnel and centrifuged to yield plasma, which is stored at -80 °C. EV size and concentration will be determined after EV purification using size exclusion chromatography (Izon, Addington, New Zealand) and nanoparticle tracking analysis (NanoSight 300, Malvern Panalytica, Worcestershire, United Kingdom) [37]. Changes in EV surface markers will be studied using the EV Array platform that simultaneous assesses up to 60 EV surface markers [38]. In addition, changes in EV content (microRNA and proteins) will be assessed using nCounter microRNA panels (NanoString, Seattle, WA, USA) and Orbitrap mass spectrometers (Thermo Fisher Scientific, Waltham, MA, USA), respectively.

At the three-month visit, an additional blood sample in a 3 mL EDTA collection tube is drawn and stored at -80 °C without centrifugation. This full-blood sample will undergo DNA extraction and APOE genotyping.

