### Sample size calculation

A previous study could show a correlation between capillary dysfunction and cognitive status in 32 patients with Alzheimer’s disease [48]. To find a similar effect size in a linear model with 10 predictor variables, a sample size of 71 patients is needed (90% power, significance level 0.05). This calculation was performed using the pwr-package in *R* version 4.3.2 [49]. Previous studies of EV characteristics were able to distinguish between stroke severity, lesion volume and outcome when comparing groups of 21 and 20 stroke patients [50]. A sample size of 100 patients with complete follow-up is therefore considered adequate.

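### The primary EV analysis groups 12-month RBANS into three bands, which costs power against the continuous score, and the 21-versus-20 precedent does not show that 100 patients suffice for it

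*Protocol article*

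**What the plan says.** The association between EV characteristics and post-stroke cognitive impairment is one of two primary objectives (Protocol article, Study objectives). Under Statistical analysis, its primary analysis is "exploring differences in EV characteristics at baseline between patients with normal cognition, impaired cognitive function" (total index 70–85) and "reduced cognitive function (total RBANS index score < 70) at 12-month follow-up using analysis of differential expression". The upper limit of the normal band's neighbour implies that normal means above 85.

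The listed secondary EV analyses are all cut-offs too: patients with a fall of at least 6 RBANS points "versus patients with no decline in total RBANS score from three to 12 months", a fall of at least 2 MoCA points, and MoCA split at 22 and at 26. No EV analysis of a continuous score is described. For CTH, the same section uses RBANS and MoCA, as change and as 12-month level, without cutting them.

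Under Sample size calculation, the formal figure (71 patients) concerns CTH. For EVs the support is that earlier work found differences when "comparing groups of 21 and 20 stroke patients", after which 100 patients with complete follow-up are called adequate. The expected split of the 100 across the three RBANS groups is not given.

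**The concern.** There are two linked problems.

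- **Sample size.** A precedent with two nearly equal groups says little about three groups whose sizes are unknown until the 12-month visit. Patients with known dementia, pre-stroke dependency, inability to consent or unfitness for follow-up are excluded, which tends to make scores below 70 rarer.
- **Efficiency.** Grouping treats 71 and 84 as the same and 84 and 86 as different. The information lost matters most where many markers are screened: the EV array alone "simultaneous assesses up to 60 EV surface markers", and microRNA and protein panels come on top.

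At stake is the chance of finding a real marker in one of the two primary objectives. Validity is not in question.

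**Working it through.** **1. The plan's own figure.** The EV part of the sample size has no effect size, alpha or power, so there is nothing to reproduce. The 71 for CTH also lacks a stated effect size. Back-solving an overall F test with 10 predictors, 90% power and alpha 0.05 gives f² ≈ 0.335, that is R² ≈ 0.25 and r ≈ 0.50. That figure does not bear on the EV analysis.

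**2. Expected group sizes.** The article gives no RBANS mean or SD. Assume a normal distribution with SD 15 and N = 100. Then n(<70) = 100·Φ((70 − m)/15), n(70–85) = 100·[Φ((85 − m)/15) − Φ((70 − m)/15)], and the rest are normal. "Kept" is the share of RBANS variance that lies between the three groups, i.e. the information retained relative to the continuous score.

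| Mean m | <70 | 70–85 | >85 | Kept |
|---|---|---|---|---|
| 100 | 2 | 14 | 84 | 46% |
| 95 | 5 | 20 | 75 | 58% |
| 90 | 9 | 28 | 63 | 68% |
| 85 | 16 | 34 | 50 | 76% |
| 80 | 25 | 38 | 37 | 80% |

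Twenty patients below 70 require a mean of 70 + 15 × 0.8416 = 82.6 or lower. The only anchor in the article is that impairment is "observed in up to 50% of stroke survivors". If that is read as 50% scoring 85 or below, the mean is 85, 16 are expected below 70, and the chance of 20 or more is 16%. With 40% or 30% at or below 85, about 10.5 or 6 are expected. The spread matters: mean 85 with SD 18 gives 20, and with SD 12 about 11.

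**3. Comparison with the precedent.** Two-sided t test, alpha 0.05, noncentrality d·√(n₁n₂/(n₁+n₂)). For 21 v 20, n₁n₂/(n₁+n₂) = 420/41 = 10.24, and 80% power needs d = 0.90. At the same d, for <70 v normal:

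- mean 85, 16 v 50: 800/66 = 12.1, power 87%
- mean 88, 12 v 58: 696/70 = 9.9, power 80%
- mean 90, 9 v 63: 567/72 = 7.9, power 70%
- mean 95, 5 v 75: 375/80 = 4.7, power 48%

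So this contrast falls short of the precedent only when the mean is above about 88, that is with fewer than about 12 patients below 70.

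**4. Three groups against the continuous score.** Simulation at N = 100 with a linear marker–RBANS relation, SD 15, 30–50% at or below 85, and six covariates (as many as the article lists for the EV analyses). The group test is a 2-df F test; the continuous test has 1 df.

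| Assumed r | Alpha | Three groups | Continuous |
|---|---|---|---|
| 0.3 | 0.05 | 53–64% | 83–84% |
| 0.4 | 0.05/60 (illustrative) | 29–42% | 76% |

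Repeat runs agree within about two percentage points. Without covariates and at mean 80, where 25 patients fall below 70, the first comparison is still 68% v 86%. The loss therefore does not depend on the lowest group being small.

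**5. Secondary point: the 6-point fall.** For a patient with no true change, P(fall ≥ 6) = Φ(−6/(15·√(2(1 − ρ)))), where ρ is retest reliability (assumed; not in the article).

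- ρ = 0.90: SD of the difference 6.71, Φ(−0.89) = 19%
- ρ = 0.75: SD of the difference 10.61, Φ(−0.57) = 29%

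Such labels dilute the contrast between decline and no decline.

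**The case against.** The other side has several sound points.

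- **The lowest group need not be under 20.** A reader might infer from the cut-offs and exclusions that it must be. The article gives no RBANS mean or SD. Its 50% figure is a frequency of impairment, not a share scoring 85 or below. Only known dementia is excluded, and patients with IQCODE above 3.48 remain. A mean of 80, or 85 with SD 18, gives 20 to 25. This stands.
- **Fewer than 20 does not mean less power than the precedent.** The normal group is larger, and step 3 shows 16 v 50 doing better than 21 v 20. Nor does the whole primary analysis rest on a handful of patients: at d = 0.90, the 70–85 v normal contrast has 96–98% power across splits of 24 v 70, 29.5 v 60 and 34 v 50. This stands.
- **The power comparison favours the proposed model.** A 1-df linear test is best when the relation is linear. A marker that shifts only below a clinical threshold would narrow or reverse the gap. The values of r and the Bonferroni level are assumptions. This stands as a condition on the size of the gain.
- **Retest error.** It is tempting to say that the decline groups are heavily misclassified, or that giving form A first and form B second moves everyone across the cut-off. Reliability and any form difference are not in the article. At ρ = 0.85, a 3-point form shift changes the share labelled as declining from 23% to 14% or 36%, which is far from everyone. A uniform shift does not vary with EV level, so it dilutes contrasts and does not create associations.
- **Exploratory wording and the unseen SAP.** The analyses are described as exploring, and the handling of multiplicity may properly be left to the SAP, so its absence here is no finding. This limits the severity. It does not change that the article names the three-group comparison as the primary EV analysis.

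**Conclusion.** The point holds in two parts. First, an earlier comparison of two groups of about 20 does not show that 100 patients are adequate for a three-group comparison of unknown split; this needs no assumption about RBANS. Second, banding the score loses material power if the marker–RBANS relation is roughly linear: about 20 to 30 percentage points at r = 0.3 and alpha 0.05, and 34 to 47 at r = 0.4 and alpha 0.05/60. Both figures rest on a normal RBANS with SD 15 and 30–50% of patients at or below 85.

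A group below 70 of fewer than 20 is likely, not established. The dilution from retest error in the 6-point definition is a secondary point that depends on the assumed reliability. The three-group analysis is inefficient, not invalid. This is a cheap improvement, not a must-fix.

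**What to change.** - Make the 12-month total RBANS index a continuous term in the same covariate-adjusted differential-expression model, and name that the primary EV analysis.
- Treat RBANS change and MoCA change as continuous in the secondary EV analyses.
- Keep the three RBANS groups and the RBANS and MoCA cut-offs as descriptive or supportive summaries.
- Remove the inference that groups of 21 and 20 make 100 patients adequate for the three-group contrast. If a justification is wanted, state the correlation detectable with 100 patients at the chosen error rate.

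The cost is wording in the analysis plan, with no added patients, visits or assays. The downside is that the model assumes an approximately linear trend and is less efficient for a pure threshold effect. The retained group summaries let that be checked.
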